#### Secondary measures

##### Sleep associated monitoring

Monitoring will be assessed using the Sleep Associated Monitoring Index (SAMI: [24]), a 30-item measure comprising of eight subscales: daytime monitoring for body sensations; calculation of time; waking monitoring for body sensations; pre-sleep monitoring for body sensations consistent with falling asleep; daytime monitoring of functioning; pre-sleep monitoring for body sensations inconsistent with falling asleep; pre-sleep monitoring the clock; and pre-sleep monitoring the environment. Items are measured on a 5-point scale on which participants indicate what is true for them over the past week (1 = not at all, 5 = all the time). Mean scores for subscales reflect total subscale scores divided by the number of items in the scale.

##### Anxiety and preoccupation with sleep

Anxiety and sleep-related worry will be examined using the Anxiety and Preoccupation about Sleep Questionnaire (ASPQ: [25]) and the Sleep Anticipatory Anxiety Scale (SAAQ: [26]). The ASPQ is comprised of 10 items that examine the extent to which participants have been worried about the nature and consequences of their sleep problem over the past 3 days. The SAAQ consists of 10 items that examine sleep-related worry and physiological aspects of anticipatory anxiety.

#### Assessment points and intervention

##### Baseline attentional bias assessment and questionnaire measures

At baseline (day 1), after blind group allocation, all participants will complete an initial measure of sleep-related attentional bias using a dot-probe task consisting of the neutral and sleep-negative word pairs. The attentional bias assessment will be delivered online using Inquisit 3.0.3.2 software (Millisecond Software, Seattle, WA, USA).

The dot-probe assessment task will consist of 384 trials in total, with 10 repetitions of 48 word pairs delivered in randomised blocks (24 sleep-negative/neutral, and 24 neutral/neutral pairs at five repetitions each). In both the experimental and control condition, each trial starts with a fixation cross appearing in the centre of the screen for 500 ms, followed by presentation of a word pair vertically aligned (3 cm separation), appearing for 500 ms. After a gap of 100 ms, a dot-probe (two small dots aligned either horizontally or vertically) appears either in the top or bottom position, remaining on the screen until a response key was pressed. Participants are specifically required to press the corresponding key, which indicated the position of the probe (key Z for left position; M for right position), as quickly and as accurately as possible. If participants responded incorrectly, error feedback will be provided triggering a 3 s delay. If a correct response is made, the screen will be cleared, and the next trial will commence after an interval of 500 ms (see Fig. 2). Here, for the initial and follow-up attentional bias assessments, the probes replace the negative and neutral member of each word pair with equal frequency to allow for the examination of vigilance and disengagement for sleep-negative stimuli.

**Fig. 2 Fig2:**
[figure not shown]
Example order of individual trial sequence for the dot-probe task. Fixation cross first presented for 500 msec, followed by word presentation side-by-side for 500 ms. After 100 ms interval, probe appears until response. If the corresponding probe location key (i.e. correct response) was pressed, no feedback is presented, and the next trial begins after 500 ms blank screen interval. However, incorrect response feedback is presented if the wrong key is pressed triggering a 3000 ms interval before the next trial begins

The modified ABM version of the task will consist of 10 repetitions of 48 word pairs delivered in randomised blocks (all sleep-negative/neutral). Here, the probe always replaces the locus of the neutral word, promoting attentional avoidance of sleep-negative stimuli. In the non-ABM control condition, all task parameters are identical to the modified ABM version, however the probes replaced the negative and neutral member of each word pair with equal frequency without promoting attention toward or away from negative words.

Following this, participants will complete: the ISI, SAMI, ASPQ, and SAAQ.

##### ABM intervention and control group procedure

On days 3–7, using a computer, participants will be required to complete a dot-probe task prior to bed. The nature of the dot-probe task will depend on group allocation. Those in the experimental treatment condition will be provided with a modified version of the aforementioned dot-probe task such that the probe only appears in the location of the neutral word. Theoretically shifting (training) their attention away from the sleep-negative words. Whereas those in the control condition will complete the same task with probes replacing the negative and neutral member of each word pair with equal frequency. Following the task, participants will complete the Pre-Sleep Arousal Scale prior to bed. On awakening, participants will be required to complete an online version of the consensus sleep diary.

##### Post ABM assessment and questionnaire measures

Following this 5-per week protocol, all participants will the complete the same attentional bias task (as completed at baseline) on the final day of the experimental phase (day 9). Moreover, the same questionnaire measures (ISI, SAMI, ASPQ, SAAQ) and sleep diary will also be completed.

##### Follow-up assessment

At follow-up (day 16) participants will again complete the ISI, SAMI, ASPQ and SAAQ. On completion, participants will be provided with an Amazon e-gift voucher for taking part. Moreover, those in the control condition will be invited to take part in the experimental treatment if willing.

#### Sample size rationale

The current power estimation was based on the meta-analysis on ABM training for anxiety conducted by Hakamata and colleagues [27] who noted a mean effect size equal to Cohen’s *d* = .61. In each group, we would require 44 participants based on a *t* test, power of .80 and an alpha level of .05 (two-tailed).

#### Statistical analyses

##### Examination of accuracy and preparation of attentional bias data

Only data from correct trials will be included in the final analysis. In addition, reaction times below 200 ms, those above 3000 ms, and those that are three standard deviations above each participant’s individual mean will be eliminated [28].

##### Calculation of vigilance and disengagement

To examine attentional bias, indices of vigilance and disengagement will be calculated. The vigilance index is calculated by subtracting the mean reaction time for negative stimuli from the mean reaction time for neutral stimuli: Vigilance index = dN,N – dT, N. Here, dN, N represents dots replacing neutral words in the presence of another neutral word (i.e. neutral: neutral-neutral trials); and dT, N for dots replacing sleep-negative words in the presence of a neutral word (i.e. congruent: sleep-neutral trial). A positive score on the vigilance index indicates faster response to dots appearing after sleep-related as compared to neutral words [24], i.e. greater vigilance for ‘negative’ stimuli. To calculate disengagement from sleep-related words, the mean reaction time for neutral trials are subtracted from the mean reaction time for trials where the dots replaced neutral stimuli in the presence of sleep-related stimuli: Disengagement index = dN, T – dN, N. Here, dN, T represents dots replacing neutral words in the presence of a sleep-related word (i.e. incongruent: sleep-neutral trials). A positive score on the disengagement index indicates slower responses to dots replacing neutral words in the presence sleep-related words [24], i.e. that attention was not directed to the neutral word but directed elsewhere (possibly the sleep-related word) when the sleep-related word is present. In sum, greater positive scores for both indices, vigilance and disengagement, are indicative of an attentional bias.

##### Analyses

First, we will examine group differences in attentional bias indices at baseline with the expectation that there should be no group difference. Following this, we will examine differences in attentional bias indices at follow-up (i.e. day 9). To examine whether any attentional bias reduced amongst the experimental group, we will then examine the group (experimental versus control) × time (baseline versus post-ABM) interaction for each index of attentional bias (i.e. vigilance and disengagement). Second, to examine whether insomnia symptoms reduced amongst the experimental group, we will examine the group (experimental versus control) × time (baseline versus post-ABM versus follow-up) interaction. Third, to separately examine whether pre-sleep cognitive arousal and sleep-onset latency reduced amongst the experimental group on nights where the tasks were completed, we will examine the group (experimental versus control) × time (days 3 vs. 4 vs. 5 vs. 6 vs. 7) interactions. Finally, to explore the secondary aim we will employ a series of Pearson’s correlational analyses to determine whether each of the attentional bias indices (i.e. vigilance and disengagement) are related to each subscale of the SAMI. Simple effects analyses will be performed to decompose any significant interactions as appropriate.

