### Participants and recruitment

We will recruit a total of 90 adult members from the general population who meet the *Diagnostic and Statistical Manual of Mental Disorders, 5*^*th*^
*edition* (DSM-5) criteria for Insomnia Disorder [19]. Potential participants will be recruited through the website ‘call for participants’ and various insomnia treatment forums and will be assessed online for eligibility. Those interested in taking part will complete the Insomnia Severity Index (ISI: [20]), and SLEEP-50 [21] measures (see ‘Questionnaire Measures’ section for more detail). Those indicating subclinical insomnia using the ISI, and do not indicate the presence of another sleep/wake disorder other than insomnia on the SLEEP-50 will be invited for a telephone interview to determine the presence of DSM-5 Insomnia Disorder. Telephone interviews will be conducted by the principal investigator (UA).

Specifically, individuals with insomnia must report dissatisfaction with sleep characterized by either a difficulty initiating or maintaining sleep or early morning awakenings. Insomnia should be present for 3 or more nights per week, for at least 3 months, and cause significant daytime impairment. Finally, these conditions must be met despite an adequate opportunity to sleep. Those who report symptoms of a sleep/wake disorder other than insomnia, an existing psychiatric illness, a central nervous system disorder, use of medication that may affect sleep, a prior head injury, pregnancy or breast-feeding or current shift-work will be ineligible to take part. Those meeting the criteria for Insomnia Disorder will be invited to participate and will be provided with an email link for the online study. All participants must have normal to corrected vision.

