### Randomisation and allocation concealment

This study will use a simple randomisation with an allocation ratio of 1:1 which will be carried out by the automated online system. As such, the research team will not be able to influence randomisation and will not have access to future allocations.

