#### Potential limitations

It is relevant to note the procedural limitations that might arise during data collection. Considering the 16-day length of this protocol, we anticipate a degree of participant dropout. In addition, considering the online delivery of ABM, some participants may experience technical difficulties in the absence of an experimenter.

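### The stated power of .80 belongs to a two-group t test, but reduction in bias is tested by a group × time interaction whose power depends on an unstated correlation; one baseline-adjusted test would secure it

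*Protocol article*

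**What the plan says.** The Sample size rationale takes its effect size from a meta-analysis of ABM for anxiety, which "noted a mean effect size equal to Cohen’s *d* = .61". It continues: "In each group, we would require 44 participants based on a *t* test", with "power of .80 and an alpha level of .05 (two-tailed"). It does not say which outcome or contrast d refers to, whether d is scaled to the post-treatment SD or the change-score SD, or what baseline to day-9 correlation is expected.

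The Analyses section sets out three steps for the bias indices, which the abstract lists among the primary outcomes:

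1. A baseline check: "we will examine group differences in attentional bias indices at baseline with the expectation that there should be no group difference".
2. A comparison of the groups at day 9.
3. The test tied to the aim of reducing bias: "we will then examine the group (experimental versus control) × time (baseline versus post-ABM) interaction for each index of attentional bias".

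No baseline-adjusted comparison is stated. Nothing says which of steps 2 and 3 governs if they disagree.

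**The concern.** The test that was powered is not the test assigned to the question. A plain two-group t test corresponds to step 2, the day-9 comparison. Step 3 has different precision: subtracting baseline removes stable differences between people but adds the noise of the baseline measurement. Which effect is larger depends on r.

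Each index is a difference between two mean reaction times in the same person, so general response speed cancels while trial noise adds. A low r is therefore possible, but the article reports no reliability or correlation.

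Two things are at stake. The .80 is not established for the test that is meant to show a reduction in bias. In addition, two efficacy tests of one outcome, with no stated priority, leave open which one the conclusion rests on.

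**Working it through.** **Inputs from the article.** d = .61, two-sided alpha .05, power .80 and 44 per group (Sample size rationale); three tests per index (Analyses).

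**Assumptions.** r is not given, so it is varied from 0 to .8. SDs are taken as equal at baseline and day 9. All figures are for 44 completers per arm and use the noncentral t distribution.

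**The stated figure reproduces.** A two-sample t test with d = .61 has power .808 at 44 per group and .798 at 43, so 44 is correct for that test.

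**Reading A: d is on the post-treatment SD.**
- Day-9 t test: effect .61, power .81 at every r.
- Interaction: Var(change) = 2σ²(1 − r), so the effect is .61/√(2(1 − r)). For example, at r = .2 it is .61/√1.6 = .482.
- ANCOVA: residual variance σ²(1 − r²), so the effect is .61/√(1 − r²), with 85 rather than 86 degrees of freedom.

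**Reading B: d is on the change-score SD.**
- Interaction: effect .61, power .81 by construction.
- Day-9 t test: effect .61 × √(2(1 − r)). At r = .7 it is .61 × √.6 = .473.
- ANCOVA: effect .61 × √(2(1 − r))/√(1 − r²) = .61 × √(2/(1 + r)). At r = .8 it is .643.

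| r | A: interaction | A: ANCOVA | B: day-9 test | B: ANCOVA |
|---|---|---|---|---|
| 0 | .52 | .81 | .98 | .98 |
| .2 | .61 | .82 | .95 | .96 |
| .4 | .73 | .87 | .87 | .92 |
| .5 | .81 | .90 | .81 | .90 |
| .6 | .89 | .94 | .72 | .89 |
| .7 | .96 | .98 | .59 | .87 |
| .8 | .99 | >.99 | .43 | .85 |

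Under reading A the interaction would need 86 per group for 80% power at r = 0, 69 at r = .2 and 52 at r = .4. It needs 44 at r = .5 and only 27 at r = .7.

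A simulation of reading A (20,000 runs per value of r) agrees:
- Interaction power: .515, .606, .807 and .957 at r = 0, .2, .5 and .7.
- ANCOVA power: .801, .814, .901 and .977 at the same values.

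**Two efficacy tests.** In the same simulation with no treatment effect, the chance that the day-9 test or the interaction reached p < .05 for one index was 8.5% at r = 0 and 9.3% at r = .7.

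**Baseline check.** Allocation is random and training starts only on day 3, so any day-1 difference is chance. With two indices, at least one such test is significant at most 1 − .95² = 9.75% of the time. This is a ceiling, reached only under independence, and the two indices share the neutral-neutral reaction time.

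**The case against.** A reader might infer that the interaction simply lacks the stated power. The documents do not support that. The shortfall needs both r below .5 and d on the post-treatment SD, and the article fixes neither. Above r = .5 under reading A the interaction exceeds the stated power, and under reading B it has it by construction. That r is low is plausible from how the indices are built, but nothing in the article shows it.

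A reader might also infer that the baseline test helps decide whether treatment worked. It does not. It is a check with no difference expected, and no covariate choice or conclusion is made to depend on it. Testing it is uninformative under randomisation, which is a minor reporting point.

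It can also be said that the article ties the aim of reducing bias to the interaction, so the day-9 test need not compete with it, and that priority may be fixed in a fuller document. That is fair, and a choice made after seeing the data is a possibility, not something the plan announces. The interaction is also a valid test in a randomised trial, so ANCOVA is a gain in efficiency and not a cure for bias.

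What remains is that the sample size argument and the stated test are not connected. Under either scaling, unless r = .5, the day-9 test and the interaction cannot both have exactly the stated power. Which one falls short, if either does, depends on quantities the article does not give.

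**Conclusion.** The point holds in conditional form. The stated .80 is correct for a two-group t test at 44 per group, but it does not carry over automatically to the interaction. With d on the post-treatment SD, interaction power runs from .52 (r = 0) through .81 (r = .5) to .99 (r = .8). With d on the change-score SD the interaction has .81, and the day-9 test drops to .72, .59 and .43 at r = .6, .7 and .8. A baseline-adjusted comparison keeps at least .80 throughout: .81 to above .99 on the post-treatment scale and .98 to .85 on the change scale. The recommendation therefore does not depend on resolving either unknown.

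These figures assume equal SDs at both times and 44 completers per arm. The margin is thin. The article says "We will recruit a total of 90 adult members from the general population", which is 90 − 2 × 44 = 2 above the requirement, and also that "we anticipate a degree of participant dropout". Its "simple randomisation with an allocation ratio of 1:1" can leave the arms unequal, so 44 in each is not guaranteed even with no losses.

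**What to change.** - **Bias indices.** Name one decisive test for each of vigilance and disengagement: the day-9 index regressed on group and baseline index (ANCOVA). If the day-9 comparison and the interaction are kept, label them supportive.
- **Baseline.** Report baseline values by group descriptively, without significance tests.
- **Insomnia Severity Index.** It is measured at baseline, day 9 and day 16, so a single-outcome regression does not carry over directly. Use a repeated-measures model of the day-9 and day-16 scores adjusted for baseline, and name the primary time point. No power calculation was made for this outcome.
- **Sample size text.** State which test and which SD the d of .61 refers to.

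The cost is wording and one degree of freedom per bias index. Baseline and day-9 indices are already scheduled, and the change itself calls for no extra participants. The Trial status section places the start of data collection in the future, so the decisive test can be fixed before any outcome is seen.

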**Methods/design:**

We propose a randomised controlled trial of 90 individuals from the general population who meet the criteria for Insomnia Disorder. Following an initial examination for the presence of a sleep-related attentional bias using the dot-probe paradigm, participants will be randomised to an online attentional bias modification training condition, or to a standard attentional bias task (non-treatment) control condition. Both conditions will be delivered online by a web platform. All participants allocated to the non-treatment control group will be offered ABM training once the study is complete. The primary outcome will be the attentional bias indices of vigilance and disengagement and self-reported insomnia symptoms, sleep onset latency and pre-sleep cognitive arousal. Attentional bias and insomnia symptoms will be assessed at baseline (day 1) and post-treatment (2 days after the final training session: day 9). Insomnia symptoms will be again assessed at follow-up (day 16). Secondary outcomes include examining whether sleep associated monitoring and worry are related to a sleep-related attentional bias in insomnia, and whether such reports reduce following ABM. All main analyses will be carried out on completion of follow-up assessments. The trial is supported by the Department of Psychology, Sociology and Politics at Sheffield Hallam University.

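### The .80 power is computed for a two-group t test, but insomnia severity is tested only by a three-time-point group × time interaction, so the stated power does not describe the ISI test

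*Protocol article*

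**What the plan says.** Sample size rationale takes its effect from a meta-analysis of ABM for anxiety, "who noted a mean effect size equal to Cohen’s *d* = .61", and concludes that in each group "we would require 44 participants based on a *t* test, power of .80 and an alpha level of .05 (two-tailed". It names no outcome, time point, within-person correlation or time profile. The recruitment target is 90 ("We will recruit a total of 90 adult members from the general population"), allocated 1:1 by simple randomisation.

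The abstract lists the ISI among several primary outcomes: "The primary outcome will be the attentional bias indices of vigilance and disengagement and self-reported insomnia symptoms". It is measured on days 1, 9 and 16. The only ISI test in the Analyses section is this: "we will examine the group (experimental versus control) × time (baseline versus post-ABM versus follow-up) interaction". On follow-on comparisons, the section says: "Simple effects analyses will be performed to decompose any significant interactions as appropriate".

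The same section does plan a direct between-arm comparison for the dot-probe indices: "we will examine differences in attentional bias indices at follow-up (i.e. day 9". It states no counterpart for the ISI.

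**The concern.** The power figure and the ISI test belong to different hypotheses. The t test asks whether the arms differ in one mean (1 df). The three-level interaction asks whether the between-arm difference varies in any way across baseline, day 9 and day 16 (2 df). Its power depends on the correlation between visits and on how the effect develops over time, and the article gives neither. One of its two degrees of freedom goes to the contrast between day 9 and day 16, which is not the question in aim (ii).

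Aim (ii) asks whether ABM lowers insomnia severity relative to control. A significant interaction does not show that by itself, because the plan names neither the time point nor the simple effect that would support the claim. Conversely, as written, no between-arm ISI comparison is planned if the interaction is not significant. The conclusion on the main clinical outcome then rests on a test whose power nobody has stated, followed by a comparison still to be chosen.

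**Working it through.** **Inputs.** From the article: d = .61, two-sided alpha .05, 44 per group, power .80 (Sample size rationale); 90 recruited at 1:1, so 45 per arm if the split is equal. My assumptions: no dropout, unit variance and the same correlation r between any two visits (compound symmetry), r = .3, .5, .7, no baseline difference, and the time profiles below.

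**1. The plan's own figure.** Two-sample t test, noncentrality d√(n/2), df 2n − 2. Exact power is .798 at n = 43, .808 at 44 and .816 at 45. The stated 44 per group is reproduced.

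**2. The planned ISI test.** The 2 × 3 interaction is F with 2 and 2(2n − 2) = 176 df. Its noncentrality is λ = (n/2) × S/(1 − r), where S is the sum of squared deviations of the between-arm differences (baseline, day 9, day 16) from their mean.
- Equal effect on both days, (0, .61, .61): S = (2/3) × .61² = .2481.
- Halved on one day, (0, .61, .305) or (0, .305, .61): S = .61²/2 = .1861.

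| r | λ, equal | power | λ, halved on one day | power |
|---|---|---|---|---|
| .3 | 7.97 | .71 | 5.98 | .57 |
| .5 | 11.16 | .85 | 8.37 | .73 |
| .7 | 18.60 | .98 | 13.95 | .92 |

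Power reaches .80 at r of about .43 for an equal effect and about .57 for one halved on one day.

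**3. What follows a significant interaction.** Simulation (20,000 trials, 45 per arm, equal effect), at r = .3, .5, .7:
- interaction plus a day-16 arm difference: .60, .72, .80
- interaction plus an arm difference on day 9 or day 16: .68, .80, .89
- interaction plus a change over time within the ABM arm: .70, .85, .98

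The spread comes from the choice of simple effect, which the plan does not make. None of these is the power of the written plan.

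**4. A single contrast adjusted for baseline.** Noncentrality is δ√(n/2)/√v, with 2n − 3 = 87 df.
- Average of days 9 and 16: v = (1 + r)/2 − r², which is .56, .50 and .36. For an equal effect, δ = .61, noncentrality is 3.87, 4.09 and 4.82, and power is .97, .98 and 1.00. Halved on one day, δ = (.61 + .305)/2 = .4575, noncentrality is 2.90, 3.07 and 3.62, and power is .82, .86 and .95.
- One day alone: v = 1 − r². With .61 present on that day, power is .85, .91 and .98. If the effect on that day is halved to .305, power is .32, .38 and .52.

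**5. Where the average does worse.** If the whole effect is on one day and none on the other, δ = .305 and the average has power .48, .53 and .66. The interaction keeps S = .2481, hence .71, .85 and .98. The average is better under the equal and halved profiles, not under every conceivable one.

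**The case against.** A group × time interaction is the conventional test of differential change in a 2 × 3 design, and means with simple effects would supply its direction. The article attaches .80 to a t test and never claims it for the interaction, so no printed number is wrong. The model and follow-up contrasts may be set out in an analysis plan that is not shown, and the words allowing simple effects as appropriate leave some latitude. Part of the gain in power shown above comes from adjusting for baseline rather than from dropping the interaction as a gate. All of this stands. What it leaves unanswered is that the article itself names both the sizing test and the ISI test, and they differ.

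Three stronger readings are tempting and are not supported:

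- A reader might infer that the ISI test is underpowered. It need not be: with an equal effect and r of .5 or more, its power exceeds .80, and nothing in the article favours a low r over a high one.
- A reader might take the interaction followed by a day-16 arm difference as the plan's own route and quote its lower figures. The Analyses section names no such step.
- A reader might cite the Background's interest in cumulative change as predicting a larger effect on day 16 than on day 9. That text concerns repeated training nights, and training runs on days 3–7, so it is complete before day 9. A halved effect on either day is an assumption of this check, not something the article predicts.

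**Conclusion.** The mismatch is real. The 44 per group is correct for the test it names, but that test is not the one planned for the ISI, so .80 cannot be read as the power for aim (ii). Under the assumptions in the check, interaction power runs from .57 to .98. It is below .80 at lower correlations or when the effect is uneven, and above it otherwise. The size of the problem cannot be fixed more closely, because r and the time profile are not stated. Any dropout would lower all these figures; Potential limitations expects some, and 90 are recruited against the 88 required.

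This merits a change, because a better-targeted test is available from data already scheduled. It is not evidence that the trial is too small.

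**What to change.** In Analyses, make the decisive ISI test one pre-specified between-arm contrast, adjusted for baseline ISI and not conditional on the interaction. Two choices are defensible:

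- **The average of days 9 and 16.** This holds up if the effect is moderately uneven, but loses power if it is confined to one day.
- **A single named day.** Day 16 can be justified by the ISI's two-week recall. At day 9 that window reaches back to 9 − 14 = day −5, before training starts on day 3; at day 16 it reaches back to day 2. The plan should then state how much power is lost if the effect fades by day 16 (.32, .38 and .52 if it halves).

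Both can come from one repeated-measures model of days 9 and 16 with baseline ISI as covariate. Keep the interaction and the separate day estimates as supportive. In Sample size rationale, say which contrast the .80 refers to. If the interaction is to remain decisive, redo the calculation for it with a stated correlation, time profile and dropout rate.

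The cost is wording only: no new visits, data or participants. The price is having to commit to one contrast in advance.

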### Questionnaire measures

#### Primary measures

##### Insomnia severity

Insomnia symptoms will be assessed using the Insomnia Severity Index [20] (ISI). The ISI consists of seven items examining the severity of insomnia symptoms over the past 2 weeks including difficulty initiating and maintaining sleep and awakening too early. Items are scored on a 5-point Likert scale, with total scores ranging from 0 to 28. Higher scores represent greater insomnia severity, with scores of ≥ 8 indicative of subclinical insomnia.

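### The ISI analysis uses day-1 ISI only as a time level; entering day-1 and screening ISI as covariates could sharpen the arm comparison (an efficiency gain, not an error)

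*Protocol article*

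**What the plan says.** At entry (Participants and recruitment), "Those interested in taking part will complete the Insomnia Severity Index (ISI: [20]), and SLEEP-50 [21] measures". "Those indicating subclinical insomnia using the ISI", and showing no other sleep/wake disorder on the SLEEP-50, go on to the telephone interview. Selection is the only use stated for this score.

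On day 1, after the dot-probe assessment (Baseline attentional bias assessment and questionnaire measures, text below Fig. 2): "Following this, participants will complete: the ISI, SAMI, ASPQ, and SAAQ". The Abstract defines baseline as day 1. The day-1 session is placed as follows: "At baseline (day 1), after blind group allocation". Training runs on days 3 to 7.

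The ISI is repeated on days 9 and 16. The Analyses section examines it by a group by "time (baseline versus post-ABM versus follow-up) interaction". No pre-training ISI score is named as a covariate.

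**The concern.** A self-reported score taken on one occasion carries noise particular to that occasion. When day 1 enters only as a time level, that noise passes into every contrast between day 1 and a later visit. As a covariate, the day-1 score is weighted by how well it predicts the outcome, which in a randomised comparison gives a residual variance no larger than that of the change score. A second pre-training score, already collected, may explain some of what remains.

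At stake is the precision of the comparison on insomnia severity, one of the primary outcomes. The trial plans 90 participants against a stated need of 44 per group, and the Potential limitations section expects some dropout, so there is little reserve.

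**Working it through.** **The plan's own figure.** Sample size rationale: d = .61, two-sided alpha .05, power .80, *t* test, 44 per group. The noncentral *t* distribution gives power .798 at 43 per group and .808 at 44, so the figure reproduces. This point does not affect it.

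**Inputs for the comparison.** The protocol gives no ISI correlation, so every r below is assumed. The outcome is one later ISI score with raw variance set to 1. The reference is a simple change from day 1. It is a yardstick only, because the planned test is an interaction over three time levels.

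**Residual variance with equal correlation r among screening, day 1 and outcome**

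- Change from day 1: 2(1 − r)
- Adjusting for day 1: 1 − r²
- Adjusting for day 1 and screening: 1 − 2r²/(1 + r)

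| r | Change | Day 1 | Day 1 + screening | Cut from using day 1 as covariate | Further cut from screening |
|---|---|---|---|---|---|
| .5 | 1.00 | .75 | .67 | 25% | 11% |
| .6 | .80 | .64 | .55 | 20% | 14% |
| .7 | .60 | .51 | .42 | 15% | 17% |
| .8 | .40 | .36 | .29 | 10% | 20% |

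**Power illustration.** With an assumed d of .4 on the raw scale (not the plan's .61), r = .7 and 45 per arm, power is .68 for the change score, .75 adjusting for day 1 and .82 adjusting for both. The first step comes from using day 1 as a covariate. Only the second belongs to the screening score, and only under equal correlations.

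**When screening predicts less well.** Fix the day-1/outcome correlation r₁ at .7, so the residual with day 1 alone is .51. Let r₂ be screening/outcome and r₁₂ screening/day 1. Then R² = (r₁² + r₂² − 2r₁r₂r₁₂)/(1 − r₁₂²). For r₂ = .5 and r₁₂ = .6, R² = (.49 + .25 − .42)/.64 = .50. The residual is .50 and the gain is .01/.51 = 2%.

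| r₂ | r₁₂ | Residual | Further cut |
|---|---|---|---|
| .6 | .65 | .474 | 7% |
| .5 | .55 | .491 | 4% |
| .5 | .60 | .500 | 2% |
| .6 | .80 | .506 | 0.9% |
| .4 | .50 | .507 | 0.7% |

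**Why the screening score may be weak here**

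- *Age.* Trial status gives 10 May 2018 for the start of recruitment and 1 November 2018 for the start of data collection, 175 days apart. The screening-to-day-1 interval is not fixed. The ISI covers "seven items examining the severity of insomnia symptoms over the past 2 weeks".
- *Selection.* Entry depends on this score (8 or more, Insomnia severity section). In a simulation assuming r = .7, SD 5 and mean 10 to 14, selection at 8 or more left a further cut of 11% to 14%. Selection limited to 8–14 left about 5%.
- *Redundancy.* If the gap is short, the two recall windows overlap and the scores may carry much the same information. The row with r₁₂ = .80 illustrates this.

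**Why not average.** With r₂ = .4 and r₁₂ = .5, the mean of the two baselines has variance (1 + 1 + 1)/4 = .75 and covariance (.7 + .4)/2 = .55 with the outcome. The change variance becomes 1 + .75 − 1.10 = .65, against .60 (8% worse). The adjusted residual becomes 1 − .55²/.75 = .597, against .51 (17% worse). Entered separately, the same two scores lose nothing in residual variance.

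**The case against.** The strongest case against is that nothing here is wrong. Day 1 is the defined baseline, the analysis uses it, and keeping an eligibility score for eligibility is ordinary practice. Covariate choice is often left to an analysis plan, which is not shown. This stands as far as it goes: the point is an improvement to an analysis that the article does state, not a defect.

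Second, the larger gains assume that screening predicts days 9 and 16 as well as day 1 does, and the long possible gap, the selection and the recall window count against that. This stands too, and is why the further gain is given as a range.

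Three stronger readings are tempting and not supported:

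- *That the screening score would certainly reduce error variance at no cost.* The documents give no correlation, the gain can be under 1%, and each covariate takes a degree of freedom.
- *That the whole rise in power from .68 to .82 is lost by ignoring screening.* About half comes from using day 1 as a covariate, and the reference is not the planned test.
- *That day-1 ISI is unusable because it follows allocation.* Allocation is described as blind, the day-1 assessment is common to both arms, and training has not begun.

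A further argument, that the screening score is available for people who miss day 1, is thin. It helps only if they still supply a day-9 or day-16 ISI, and nothing suggests this would be common.

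The losses shown for averaging do not count against the proposal, which keeps the scores separate.

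**Conclusion.** The point holds as an optional gain in efficiency. Using day-1 ISI as a covariate is the firmer part: a 10% to 25% cut in error variance relative to a simple change score, for assumed correlations of .8 down to .5. Adding screening ISI may cut a further 11% to 20% if it predicts as well as day 1, and perhaps only 1% to 5%, or less, if it is old, range-restricted or redundant. All sizes rest on assumed correlations. Selection on the screening score precedes training and falls on both arms alike, so it limits the gain without biasing the comparison. Neither the validity of the planned test nor the stated sample size is in question.

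**What to change.** In the Analyses section, state that the between-arm difference in day-9 and day-16 ISI will be estimated with an ANCOVA or mixed model that adjusts for day-1 ISI, with screening ISI as a separate additional covariate. State also that the two scores will not be averaged and that screening will not become an extra level of time, since that would change the interaction being tested. Specify this before outcomes are analysed, so that the covariates are not a post hoc choice.

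The cost is a sentence of wording and one degree of freedom per covariate (from 88 residual degrees of freedom with 90 participants to 87, then 86). No new data or visits are needed. Little gain should be expected from the screening score where the screening-to-day-1 gap is long. If most gaps prove long, adjusting for day 1 alone keeps most of the benefit.
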